#### Power calculation and sample size

The sample size was calculated using statistical software (G*Power 3.1.5) on the main outcome measure, fasting serum insulin concentration. This calculation was based on data from a hand-cycling training group, which reported an improvement of −14.3 ± 12.7 pmol l^−1^ [59] in fasting insulin over 16 weeks. Based upon these data (Cohen’s *d* = −1.1) it was estimated that nine participants are required to detect a statistically significant change in insulin sensitivity in the INT group. The power was 0.8 and the alpha was set at 0.05. As a 2:1 ratio is to be adopted, a computer programme (www.statstodo.com/SSizUnequal_Pgm.php) was used to calculate sample size adjustments for two groups with unequal size, to account for any consequences of unequal allocation on statistical power [99]. Also, taking into account an expected drop-out rate of approximately 15 %, we aim to recruit at least 24 (INT: 16, CON: 8) participants with chronic paraplegia.

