The current literature on PA research for individuals with SCI has recently been systematically classified [55]. Most studies between 2000 and 2012 have been categorised as either: phase 1 (linking PA and health outcomes); phase 2 (validating or developing PA monitors) or; phase 3 (identifying factors influencing behaviour or examining theories of behaviour change). Such categorisation implies that this field is in the early stages of development and research should now focus on phase 4 (evaluating interventions) and phase 5 (disseminating health promotion policies and translating research into practice). Due to the inconsistent findings across studies, concluded via a systematic review requested by the Consortium for Spinal Cord Medicine [56], it would appear that current evidence is insufficient to determine whether exercise improves carbohydrate and lipid metabolism disorders among adults with SCI. However, previous studies have demonstrated that arm-crank exercise improves lipid profiles [57], inflammatory biomarkers [58] and fasting insulin concentrations [59] with interventions ranging from 12 to 16 weeks in duration. It is possible that inconsistencies in the current literature may be caused by considerable heterogeneity in study participants, the type of exercise programme and/or the outcome measures examined. Here we describe the study design for a randomised controlled trial (RCT) with a homogeneous cohort, examining a variety of outcome measures not simply confined to physical capacity, that will contribute towards our understanding of how a home-based upper body exercise intervention might impact metabolic, cardiovascular and immunological health in individuals with SCI: the HOMEX-SCI study.

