### Objectives

The primary objective of the HOMEX-SCI study is to assess the impact of a 6-week home-based moderate-intensity arm-crank exercise intervention on markers of metabolic and cardiovascular health in inactive individuals with chronic SCI. Little is known about the impact of a moderate- to vigorous-intensity exercise intervention on messenger ribonucleic acid (mRNA) expression of adipose tissue, which is surprising considering that it is a major site for energy storage. To our knowledge, adipose tissue biology has never been studied in a cohort of individuals with SCI. Thus, a secondary objective is to investigate at baseline, and following intervention, the expression of genes within adipose tissue that are associated with a variety of biological processes such as energy homeostasis, glucose metabolism, lipid metabolism and inflammatory responses. Other objectives include: characterising aspects of adaptive immune function pre and post intervention, quantifying changes in body composition, aerobic capacity, dietary and physical activity behaviours and various constructs of health and wellbeing. The exercise intervention group’s responses, for all outcome measures over 6 weeks, will be compared to a control group.

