## Methods

### Study design

This study is a pre-post, parallel-group design, with participants randomly assigned to a 6-week home-based exercise intervention (INT) or a control period (CON). The planned experimental design is summarised below (Fig. 1), consistent with current Consolidated Standards of Reporting Trials (CONSORT) guidelines [60]. The South West (Exeter) National Research Ethics Service Committee has approved this study protocol (REC reference number 14/SW/0106) and the trial has been registered as a current controlled trial (ISRCTN57096451). Upon initial contact (by email or telephone), the study will be described briefly and those interested in enrolling will be asked to read a detailed participant information sheet and complete a health screen questionnaire. Interested individuals will be screened via a telephone conversation 48 hours after their initial contact to ascertain eligibility. A focus will be placed on establishing a good rapport at this initial contact and also as individuals progress through the enrolment process. Written consent will be obtained during the initial laboratory visit and participants will be informed that they can withdraw from the study at any time without consequence.

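### The stated power of 0.8 applies a 16-week fasting-insulin effect at full size to a 6-week intervention, and the plan neither states nor justifies that assumption

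*Protocol article*

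**What the plan says.** The section on power calculation and sample size works "on the main outcome measure, fasting serum insulin concentration". Its effect comes from the training group of an outside study, which "reported an improvement of −14.3 ± 12.7 pmol l^−1^ [59] in fasting insulin over 16 weeks". The article converts this to a standardised effect of 1.1 in absolute size. From it the article derives nine participants to detect a change in the exercise group (INT), with power 0.8 and alpha 0.05. It then adjusts for 2:1 allocation and about 15% dropout, and plans 24 participants: 16 INT and 8 control (CON).

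The primary objective is to "assess the impact of a 6-week home-based moderate-intensity arm-crank exercise intervention on markers of metabolic and cardiovascular health". The same section says that INT responses will be compared with a control group, and the statistical analysis section plans a group-by-day ANOVA.

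The background says that earlier arm-crank studies showed benefit, fasting insulin included, "with interventions ranging from 12 to 16 weeks in duration". The Discussion says that improvement is expected over the 6-week course and that the weekly amount of exercise was chosen to be substantial. It gives no size for the expected 6-week change.

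**The concern.** The effect in the power calculation was seen over 16 weeks, and the effect to be measured arises over 6 weeks. Entering the 16-week value unchanged assumes that the whole change in fasting insulin has appeared by week 6, or that this programme achieves as much in less time. The article states neither assumption and gives no evidence for the size.

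What is at stake is the reading of the result. The 0.8 is printed without a condition. If the 6-week effect is smaller, the real power is lower, and a non-significant result set against a nominal 0.8 would look like stronger evidence of no benefit than the design can supply. The Discussion hopes that the findings may inform activity guidelines, so the strength of a null result matters.

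**Working it through.** **Inputs.** From the power section: mean change 14.3 pmol/l (a fall), SD of change 12.7, alpha 0.05, power 0.8, n = 9, planned 16 INT and 8 CON, dropout about 15%. From the study design section: intervention length 6 weeks. Assumed here: a two-sided test (sidedness is not stated, but two-sided returns exactly nine and one-sided returns seven), and an SD of change that is the same at 6 weeks. The fraction f of the 16-week effect reached by 6 weeks is not in the document and is varied.

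**Step 1: reproduce the plan's nine.** d = 14.3 / 12.7 = 1.126, printed as 1.1. For a paired t test on change, power comes from the noncentral t distribution with n − 1 degrees of freedom and noncentrality d√n.
- d = 1.1: n = 8 gives 0.761, n = 9 gives 0.823.
- d = 1.126: n = 8 gives 0.779, n = 9 gives 0.840.

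Nine is therefore the smallest n that reaches 0.8, and it belongs to a within-INT test. One route to the total also reproduces. Nine per group at equal precision under 2:1 gives 9 × (1 + 2)/2 = 13.5 INT and 6.75 CON, or 20.25 in all; 20.25 / 0.85 = 23.8, so 24.

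**Step 2: share of the effect needed for 0.8, within INT.** Solve for the d that gives power 0.8, then divide by 1.126. After dropout, INT is 16 × 0.85 = 13.6, so 13 to 14.

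| INT n | d needed | pmol/l (d × 12.7) | share of 14.3 |
|---|---|---|---|
| 9 | 1.067 | 13.6 | 95% |
| 13 | 0.847 | 10.8 | 75% |
| 14 | 0.810 | 10.3 | 72% |
| 16 | 0.749 | 9.5 | 67% |

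**Step 3: the INT versus CON comparison.** With two test days, the group-by-day interaction is equivalent to a two-sample t test on change. The noncentrality is d√(ab/(a + b)) for arms of a and b, with a + b − 2 degrees of freedom. Assume no change in CON and a common SD of 12.7. CON after dropout is 8 × 0.85 = 6.8, about 7.
- 16 v 8: 0.8 needs d = 1.269, which is 1.269 × 12.7 = 16.1 pmol/l, or 113% of 14.3.
- 14 v 7: 0.8 needs d = 1.367, which is 1.367 × 12.7 = 17.4 pmol/l, or 121% of 14.3.

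**Step 4: power by share of the effect reached at 6 weeks** (d = f × 1.126).

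| f | within INT, n = 9 | within INT, n = 14 | INT v CON, 16 v 8 | INT v CON, 14 v 7 |
|---|---|---|---|---|
| 100% | 0.84 | 0.97 | 0.70 | 0.64 |
| 75% | 0.60 | 0.83 | 0.46 | 0.41 |
| 50% | 0.32 | 0.50 | 0.24 | 0.21 |

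**The case against.** Using the nearest published effect is ordinary practice in a small field, and the article is open about its 16-week origin. The Discussion gives a reason for the shorter course: four sessions of 45 minutes a week, against a typical two to three sessions. It also notes that earlier programmes ran from as little as 5 weeks. The 12 to 16 weeks in the background describe the studies that found benefit, and do not say that shorter training fails. The analysis section plans effect sizes and magnitude-based inferences, so interpretation will not rest on significance alone. All of this stands, and it limits the point. It leaves one gap: the reasons offered concern direction and weekly amount, not whether 14.3 pmol/l is reached by week 6.

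Three stronger readings are tempting, and the document does not support them.
- A reader might infer that the trial keeps 0.8 only if 95% of the effect appears by week 6. That figure describes the nine-participant calculation. With 13 to 16 in INT the within-group test tolerates losing a quarter to a third of the effect.
- A reader might infer that the time mismatch is what takes the INT versus CON comparison below 0.8. Under the assumptions above, that comparison is already below 0.8 with the whole 16-week effect. A smaller 6-week effect lowers it further.
- A reader might infer that 6 weeks delivers too little exercise to match the source study. The document does not give that study's session frequency or length, so the two amounts cannot be compared.

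**Conclusion.** The point holds in a limited form. The printed 0.8 depends on an unstated assumption that a 16-week effect applies in full at 6 weeks. How much that matters depends on the test. The within-INT test at the planned size has a real margin, and 0.8 survives down to about 67 to 75% of the effect. The INT versus CON comparison, which the objectives call for, has no margin: power is 0.64 to 0.70 at full effect and 0.21 to 0.24 at half.

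These figures assume a two-sided test at 0.05 and an SD of change of 12.7 pmol/l at 6 weeks. The between-group figures also assume no mean change in CON and the same SD in both groups. The article expects less variability in CON, so the common SD is a simplification. The true 6-week share is unknown from this document. The lower rows illustrate a range and are not a forecast that the effect will be halved. The consequence is a limit on what a null 6-week result can show, and it does not make the design invalid.

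**What to change.** In the power calculation and sample size section:
- State that the 0.8 assumes the 16-week effect size applies after 6 weeks.
- Replace the single figure with a short table of power for 50 to 100% of that effect, at 16 and 8 and after dropout, for both the within-INT and the INT versus CON comparison.
- Give the smallest between-group 6-week change detectable with 80% power, about 16 to 17 pmol/l under the assumptions above.
- Say that a non-significant 6-week result will be interpreted by its confidence interval, and not against the 0.8.

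The cost is a few sentences and a small table. Enrolment, intervention and schedule stay as they are, which suits a trial that reports 21 of 24 recruited. The only downside is a less favourable stated power.

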After baseline laboratory testing and habitual free-living monitoring, the first nine participants will be randomly allocated to the experimental group (INT) or the CON group using a block randomisation plan (fixed block size of nine; allocation ratio of 2:1; no stratification). Randomisation will be performed by an independent researcher using a concealed list generated with a web-based platform (www.randomization.com). Within a highly heterogeneous population such as individuals with SCI, we decided to use minimisation [67] to ensure balance between the two groups for baseline characteristics (age, body mass, level of spinal cord lesion and physical activity level). Subsequent participants who enrol on the trial will, therefore, be allocated to either the INT group or the CON group in order to balance the groups in these variables of interest. We opted for an unequal allocation ratio as it has been supported as an alternative approach for ‘confirmatory trials’ [68, 69], primarily to increase the amount of data on the INT, where individual responses are likely more variable. We presume limited variability in the CON group, as participants will continue to live their normal lifestyle. Any small loss of precision with the use of unequal allocation has been appropriately accounted for in the sample size calculation. While participants may have a strong preference to receive the INT and not be in the CON group, we will try to overcome this by offering a waiting-list control. Participants in the CON group will, therefore, be offered the opportunity to participate in the INT once they have completed the CON period.

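### The nine participants and 0.8 power apply to a pre-post change within INT, not to the INT-versus-CON comparison the trial makes, for which no power is given

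*Protocol article*

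**What the plan says.** The section Power calculation and sample size bases the calculation "on the main outcome measure, fasting serum insulin concentration". The effect comes from a single arm of an earlier study: "This calculation was based on data from a hand-cycling training group, which reported an improvement of" 14.3 with SD 12.7 pmol/l over 16 weeks, expressed as Cohen's d of -1.1. From this, "it was estimated that nine participants are required to detect a statistically significant change in insulin sensitivity in the INT group". Power is 0.8 and alpha 0.05. The section then reports an adjustment for two groups of unequal size and an allowance of about 15% for drop-out, and concludes: "we aim to recruit at least 24 (INT: 16, CON: 8) participants with chronic paraplegia".

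The Objectives section says that the intervention group's responses "for all outcome measures over 6 weeks, will be compared to a control group". The Statistical analysis section plans a two-way mixed ANOVA, group (INT, CON) by day (baseline, follow-up).

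Under Recruitment and randomisation, the article presumes that variability in CON is limited, without a figure, and states: "Any small loss of precision with the use of unequal allocation has been appropriately accounted for in the sample size calculation".

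**The concern.** The effect size is a one-sample quantity: the mean change in one group divided by the SD of change in that group. A sample size derived from it answers whether INT changes from its own baseline. The trial asks whether INT changes more than CON. The estimate for that question also carries the sampling error of the CON mean change. With equal SDs and equal group sizes, the variance of the difference is twice that of one group's mean change.

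The later adjustment for two unequal groups only makes sense if its starting number is a per-group number for a two-group test. The nine is not such a number. A reader who sees 0.8 power followed by a two-group adjustment will naturally take 24 as giving 0.8 for INT versus CON on the main outcome, and nothing in the article supports that. At stake is how informative the trial's main comparison can be said to be, particularly if the interaction is not significant.

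**Working it through.** **Inputs.** From the sample size section: mean change 14.3 and SD of change 12.7 pmol/l in one group, d = 1.1 as rounded there (14.3/12.7 = 1.126 unrounded), power 0.8, alpha 0.05, ratio 2:1, drop-out about 15%, target 16:8. Sidedness is not stated. Neither a CON SD of change nor a CON mean change is given.

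**Step 1: reproduce the nine.** For a one-sample (paired) t test the noncentrality is d × √n on n − 1 degrees of freedom. Two-sided 5%, exact noncentral t:

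| n | d = 1.1 | d = 1.126 |
|---|---|---|
| 8 | 0.761 | 0.779 |
| 9 | 0.823 | 0.840 |

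Nine is therefore the smallest n reaching 0.8. The alternatives do not give nine: a one-sided paired test needs 7, a two-sided two-sample test at 1:1 needs 14 to 15 per arm, and a one-sided two-sample test needs 11 per arm.

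**Step 2: from nine to 24 (inferred).** Treat nine as the per-group size of a 1:1 trial and convert to 2:1 at the same precision:

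- INT: 9 × 3/2 = 13.5. CON: 9 × 3/4 = 6.75. Rounded, 14 + 7 = 21.
- Drop-out: 13.5/0.85 = 15.9 and 6.75/0.85 = 7.9, that is 16 + 8 = 24.

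The conversion itself is sound: 13.5 × 6.75/20.25 = 4.5, the same as 9 × 9/18 = 4.5. But nine per group in a two-sample test has power of only 0.592 (d = 1.1) to 0.612 (d = 1.126). The 2:1 step preserves the precision of a base number that was never large enough for this contrast.

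**Step 3: power for the contrast tested.** With two days, the group-by-day interaction equals a pooled two-sample t test on change scores. The noncentrality is d × √(n1·n2/(n1 + n2)) on n1 + n2 − 2 degrees of freedom. At 14:7 and d = 1.126 this is 1.126 × √(98/21) = 2.43. Assuming that CON has SD 12.7 and mean change zero, two-sided 5%:

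| INT:CON | d = 1.1 | d = 1.126 |
|---|---|---|
| 14:7 (after drop-out) | 0.616 | 0.636 |
| 16:8 (no drop-out) | 0.680 | 0.700 |
| 20:10 | 0.783 | 0.801 |
| 22:11 | 0.823 | 0.840 |

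At 14:7 the standardised difference detectable with 80% power is 1.367, that is 1.367 × 12.7 = 17.4 pmol/l, against the 14.3 used for sizing. By comparison, the within-INT paired test with 14 completers has power of about 0.97.

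**Step 4: sensitivity to the CON SD.** Simulated at 14:7 with an effect of 14.3 and no mean change in CON:

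| CON SD / INT SD | Pooled (as in the ANOVA) | Welch |
|---|---|---|
| 1.0 | 0.64 | 0.61 |
| 0.75 | 0.72 | 0.77 |
| 0.5 | 0.79 | 0.90 |
| 0.4 | 0.82 | 0.93 |

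**The case against.** The strongest reply is that the 62-64% is not a consequence of the article's inputs alone. It needs a CON SD equal to INT's, whereas the only thing the article says about CON is that its variability is presumed limited. If the CON SD were half of INT's, the pooled test would have about 79% power, close to the nominal level, and at 0.4 it would pass 80%. This stands, and it is why the shortfall should be given as a range. It does not remove the point, because no CON SD is stated and the sample size calculation uses none.

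The article also says openly that the nine are for a change in INT and never claims 0.8 for INT versus CON. That stands too. The defect is a mismatch between the contrast sized and the contrast tested, not a false between-group figure. The route from nine to 24 is likewise a reconstruction, since the program's inputs and output are not shown.

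One-sided testing is no rescue. A one-sided two-sample test at 16:8 and d = 1.126 reaches 0.809, but only with no drop-out, and one-sided testing does not reproduce the nine.

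A reader might infer that the sizing invites a retreat to the within-INT change if the interaction is not significant. The analysis section does not support this: the follow-up t tests are run only where a significant interaction is found, with a Holm-Bonferroni adjustment.

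**Conclusion.** The point holds as a mismatch. The nine and the 0.8 belong to a two-sided paired test within INT, while the trial's objective and analysis are the INT-versus-CON group-by-day comparison, whose power is not stated.

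Its size depends on an unstated CON SD. Assuming an effect of 14.3 pmol/l, no mean change in CON, two-sided 5% and the pooled analysis, power with 14:7 completers is about 62-64% if the SDs are equal, 72% if CON's is 0.75 of INT's, and 79% if it is half. With all 24 completing and equal SDs it is 68-70%. It would be too strong to say that the article's own inputs fix the power at 62-64%, because the equal-SD assumption is added here.

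The statement that unequal allocation was appropriately accounted for is sound at most for the 2:1 conversion itself, and appears to rest on a base number taken from the wrong test.

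**What to change.** In Power calculation and sample size:

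- State that the nine participants and the 0.8 refer to the pre-post change within INT.
- Add the power for the INT-CON difference in change with about 21 completers (14:7), naming the assumed CON SD and mean change: about 62-64% with equal SDs and no CON change, and about 72% and 79% for CON SDs of 0.75 and 0.5 of INT's. Give the detectable difference that matches the chosen assumption (17.4 pmol/l at 80% power with equal SDs).
- Replace insulin sensitivity with fasting insulin in the sentence on the nine participants, since that is the outcome used for sizing. This does not change any number.

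In Recruitment and randomisation, correct the claim about unequal allocation. If the route in Step 2 is confirmed, say that the 2:1 adjustment was applied to a sample size derived for a within-group test.

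The cost is wording only, and a less favourable power statement. With 21 of 24 already recruited at the time of writing, no extra participants and no change to conduct or analysis are needed.

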## Discussion

To our knowledge, this will be the first study to simultaneously evaluate the efficacy of a home-based arm-crank ergometry exercise intervention and explore the biological mechanisms of action in persons with chronic SCI. Considering the aforementioned barriers to engage in PA, a convenient and accessible form of exercise is necessary to maximise exercise compliance in this population. A 16-week laboratory-based RCT [59], which experienced large drop-out rates, has recently advocated that researchers should consider how to make exercise interventions more feasible to individuals with SCI. Home-based arm-crank ergometer exercise has been examined in other hard-to-reach groups (polio patients) [100] and will overcome transportation barriers and the lack of accessible exercise equipment. Changes in outcome measures with increased PA, achieved through enhanced compliance, may indicate that home-based arm-crank exercise has the potential to be used as a more long-term behavioural strategy to improve clinical outcomes and quality of life in persons with SCI.

Various exercise intervention protocols have been employed for individuals with SCI previously, including arm-crank ergometry [101], functional electrical stimulation (FES) [102] or wheelchair propulsion [103] ranging from between 5 to 57 weeks in duration. The frequency of exercise in these studies was typically between two and three sessions per week lasting 30 to 60 minutes per session. We settled on the proposed intervention of 6 weeks of arm-crank exercise, 4 × 45 minutes per week, in order to provide a considerable exercise stimulus. Over this time-course we expect to see improvements in our primary outcome measure of metabolic control, irrespective of weight loss (which may be negligible as a result of a compensatory increase in energy intake) [104].

Previous work has demonstrated that genes expressed in skeletal muscle, related to both ‘insulin action’ and ‘adipocytokine signalling’ pathways, are downregulated after 3 weeks of deconditioning in able-bodied males and upregulated after 6 weeks of FES exercise training in individuals with paralysis [105]. Building on these findings, we speculate that 6 weeks of arm-crank exercise will elicit favourable alterations in the expression of key genes involved in energy homeostasis, glucose metabolism, lipid metabolism and inflammatory pathways in adipose tissue. By examining the expression of genes involved in a variety of biological pathways, we hope to further our understanding of the mechanisms whereby PA might influence metabolic control and inflammation in this population.

It is well established that high levels of habitual PA and/or undertaking structured bouts of exercise can improve aspects of immune function in healthy individuals without a disability [48, 49, 106, 107]. However, it is unknown whether these findings generalise to people with SCI. Considering that: individuals with SCI exhibit less robust immunity compared to regularly active, lean and able-bodied people [50]; and that impaired immune function has been reported in sedentary overweight individuals without a disability [45–47], then it is possible that disability-associated impairments in immune function are brought about by sedentary behaviour and adipose tissue accumulation/deregulation. This idea has never been investigated. In the proposed work, we will examine the magnitude of anti-viral cell-mediated immunity (i.e. T cell IFN-γ production) in resting samples pre and post intervention. This response is a functionally relevant and readily observed measure of host immunity that can be assessed sensitively with robust methodology.

The findings from this study might help to inform new evidence-based PA guidelines specific to individuals with a chronic SCI. By taking a holistic approach that addresses a number of relevant outcome measures in a single study, using a rigorous research design (RCT with true control group), this study is in accordance with recent recommendations [56, 108]. The results will also act as a scientific platform for further interventional studies in other diverse and at-risk populations.

